**Secondary and exploratory outcome variables***			
The different variables being part of the primary safety composite outcome will even be studied individually in the form of exploratory analyses.			
Stillbirth defined as intrauterine foetal death of a fetus that was alive at time of randomisation	Dichotomous (yes, no)	ICD-10 O36.4	SPR
Neonatal death of a live born child that dies days 0–27, not including accidents	Dichotomous (yes, no)	SNQ 2101, 2103	SNQ, SCB, the Cause of Death Register
Apgar score <4 at 5 min	Dichotomous (yes, no)	SNQ 421, SPR “Apgar5”	SNQ, SPR
pH <7.00 or base deficit >15 mmol/L in the umbilical artery	Dichotomous (yes, no)		SNQ, SPR
Severe birth asphyxia	Dichotomous (yes, no)	ICD-10 P21.0	SNQ, SPR
Hypoxic ischaemic encephalopathy II–III	Dichotomous (yes, no)	ICD-10 P91.6B or C or tick box	SNQ
Intracranial haemorrhage	Dichotomous (yes, no)	ICD-10 P10, P52	SNQ
Neonatal convulsions	Dichotomous (yes, no)	ICD-10 P90	SNQ
Therapeutic hypothermia	Dichotomous (yes, no)	ICD-10 P80.8, P80.9, DV034	SPR, SNQ
Meconium aspiration syndrome	Dichotomous (yes, no)	ICD-10 P24.0	SNQ, SPR
Mechanical ventilation within first 72 hours	Dichotomous (yes, no)	Procedure code DG021, DG022, DG002	SNQ
Neonatal pneumonia	Dichotomous (yes, no)	ICD-10 P23	SNQ
Neonatal sepsis	Dichotomous (yes, no)	ICD-10 P36	SNQ
NICU admission >48 hours	Dichotomous (yes, no)		SNQ
Further outcomes for the child			
Obstetric brachial plexus injury	Dichotomous (yes, no)	ICD-10 P14.0, P14.1, P14.3, P14.8, P14.9	SNQ, SPR
Admission to the NICU	Dichotomous (yes, no)		SNQ
Time at NICU	Continuous (days and hours)		SNQ
Treatment for hypoglycaemia	Dichotomous (yes, no)	ICD-10 P70.3 P70.4A-B, P70.8, P70.9	SNQ, SPR
Readmission after delivery due to the child’s health until day 27 after delivery	Dichotomous (yes, no)		SNQ
Healthy person accompanying sick person (mother stays at the hospital due to need of care for the newborn) until day 27 after delivery	Dichotomous (yes, no)	ICD-10 Z76.3	SPR
Apgar score <7 at 5 min	Dichotomous (yes, no)	SNQ 241, SPR “Apgar5”	SNQ, SPR
Further outcomes for the mother within 12 weeks from delivery if not specified otherwise			
Vaginal delivery (spontaneous vs instrumental)	Dichotomous (yes, no)	Tick box Spontaneous vaginal ICD-10 O80 Instrumental vaginal ICD-10 O81 Procedure code MAF00, MAF10, MAF96, MAC23 MAE00, MAE03, MAE20, MAE96	SPR

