Placental abruption	Dichotomous (yes, no)	ICD-10 O45	SPR
Number and reasons of visits and phone calls to the hospital in the outpatient group (balloon catheter expulsion, planned visit after 24 hours, PROM, pain, vaginal bleeding, contractions, impaired urination, foetal movements, delivery before reaching the hospital, other)			eCRF, SPR, the National Patient Register and regional registries as for example, VEGA (Vårddatabas för Enskilda patienter, Grupper och Analyser) in the Western Healthcare region
Need of additional induction method	Dichotomous (yes, no)	ICD-10 O61.X	eCRF, SPR
Infection (before, during, after delivery)	Dichotomous (yes, no)	ICD-10 O75.3, O85, O86, O91, O98, and see below	SPR, the National Patient Register, Prescribed Drug Register
Chorioamnionitis	Dichotomous (yes, no)	ICD-10 O41.1, SNQ 303	SPR, SNQ,
Urinary tract infection	Dichotomous (yes, no)	ICD-10 O86.2	SPR, the National Patient Register, Prescribed Drug Register
Endometritis	Dichotomous (yes, no)	ICD-10 O85.9, O86.1 O86.3, O86.8	SPR, the National Patient Register, Prescribed Drug Register
Wound infection	Dichotomous (yes, no)	ICD-10 O86.0	SPR, the National Patient Register, Prescribed Drug Register
Sepsis	Dichotomous (yes, no)	ICD-10 A41	SPR, the National Patient Register, Prescribed Drug Register
Fever during delivery	Dichotomous (yes, no)	ICD-10 O75.2	SPR
Fever postpartum	Dichotomous (yes, no)	ICD-10 O86.4	SPR
Need and method of pain relief during delivery		ICD-10 ZXH50, ZXH40, ZXH10, SN999	SPR
Episiotomy	Dichotomous (yes, no)	Tick box (left, median, right) Procedure code TMA00	SPR
Grades 3 or 4 perineal laceration	Dichotomous (yes, no)	Tick box sphincter, rectum ICD-10 O70.2, O70.3, MBC33	SPR
Perineal laceration	Dichotomous (yes, no)	Tick box, ICD-10 O70	SPR
Amount of postpartum bleeding	Continuous (mL)		SPR
Postpartum bleeding >1000 mL	Dichotomous (yes, no)	ICD-10 O72	SPR
Transfusion	Dichotomous (yes, no)	Procedure code DR029, DR030, DR036-039	SPR
Breastfeeding at discharge from hospital	Dichotomous (yes, no)		SPR
Breastfeeding at follow-up visit to the midwife at 8–12 weeks postpartum	Dichotomous (yes, no)		SPR
Readmission after delivery due to the mother’s health	Dichotomous (yes, no)		SPR, the National Patient Register
Experience of delivery	Continuous 1–10 Categorical		SPR
Postnatal depression	Dichotomous (yes, no)	ICD-10 F53.X	SPR
Time variables			
Time from start of induction to second stage of delivery	Continuous (hours, minutes)		SPR

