#### Acceptability and experience of outpatient IOL

Further, outcomes relating to the acceptability and experience of the woman, her partner and the care providers will be studied:

Questionnaires measuring general self-efficacy (GSE),^32^ health-related quality of life (HRQL) (EuroQol Visual Analogue Scale (EQ-VAS) and EuroQol 5-Dimension (EQ-5D)),^33 34^ sense of coherence (SOC-13),^35^ pain catastrophising (PCS)^36^ and depression (The Edinburgh Postnatal Depression Scale, EPDS)^37^ at baseline are sent out by email and/or short message service (SMS) to women and partners after inclusion, but before randomisation. Three months after delivery, the GSE, EQ-VAS, EQ-5D, SOC, PCS, EPDS, childbirth experience questionnaire (CEQ2),^38^ father for the first-time questionnaire (FTFQ)^39^ and Breastfeeding Self-Efficacy Scale Short Form (BES-SF)^40^ are distributed by email and/or SMS. Furthermore, the experience of IOL will be evaluated by a questionnaire adapted from Bollapragada *et al*,^41^ allowing participants to provide free-text responses. Partners at one centre are invited to a web-based qualitative questionnaire adapted from Daniels *et al*^42^ 3 months after delivery. In all participating partners, background characteristics (age, education level, number of children and number of experienced childbirths and IOL) are registered. All questionnaires are validated in Swedish and English.

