### Data collection, management, and analysis

#### Data collection

Data will be collected from Swedish quality and mandatory health registers, the study eCRF and questionnaires. Data from the different sources will be linked through the Swedish personal identification number before being replaced by a study ID. Register data will be collected from SPR,^26^ the Swedish Neonatal Quality Register (SNQ),^44^ the Swedish Ambulance Register,^45^ registers at the National Board of Health and Welfare (National Patient Register, the Cause of Death Register, the Prescribed Drug Register)^46^ and Statistics Sweden (SCB),^47^ see table 2. All registers have close to full coverage due to electronic data transfer from hospital charts.

For data collection in the questionnaire and interview part of the study, please see above.

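### Table 3 takes coded postnatal depression from the Swedish Pregnancy Register alone, although the linked National Patient Register is used for comparable maternal outcomes

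*Protocol article*

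**What the plan says.** Table 3 of the protocol article (secondary and exploratory health outcomes) gives each variable a type, a description and a source. The row "Postnatal depression" is dichotomous, described by ICD-10 F53.X, with SPR as the only source. It falls under the block headed "Further outcomes for the mother within 12 weeks from delivery if not specified otherwise", and the row sets no other window.

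Several other rows in that block have wider sources. For infection, urinary tract infection, endometritis, wound infection and sepsis the source is "SPR, the National Patient Register, Prescribed Drug Register". Thrombosis and pulmonary embolism have the same three. Stroke, cardiac arrest and maternal readmission have SPR and the National Patient Register.

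The Data collection section names the linked registers of the National Board of Health and Welfare as the "National Patient Register, the Cause of Death Register, the Prescribed Drug Register". It says of the registers in general: "All registers have close to full coverage due to electronic data transfer from hospital charts".

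Separately, the section on acceptability and experience sends women the EPDS before randomisation and again three months after delivery. It belongs to a different set of outcomes, introduced with the words "outcomes relating to the acceptability and experience of the woman, her partner and the care providers will be studied". The Table 3 row does not refer to it.

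**The concern.** Postnatal depression arises after birth, so within a 12-week window it can be diagnosed after the woman has left the maternity hospital. For other events of that kind Table 3 adds the National Patient Register. For this one it does not, and the article gives no reason. A diagnosis recorded only in the patient register would be counted as no event.

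The Data analyses section reports a risk difference and a risk ratio, each with a 95% CI, for dichotomous outcomes. Incomplete capture affects the two differently. A small absolute difference with a narrow interval could be read as reassurance about maternal mental health when part of the smallness comes from how the outcome was found.

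**Working it through.** **Is there a figure to reproduce?** No. The article gives no prevalence, no sensitivity of F53.X in SPR and no power for this outcome. The check is a comparison of rows, followed by algebra and an illustration on assumed values.

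**Step 1. Sources of comparable rows in Table 3**

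| Maternal outcome | SPR | National Patient Register | Prescribed Drug Register |
|---|---|---|---|
| Infection; urinary tract infection; endometritis; wound infection; sepsis | yes | yes | yes |
| Thrombosis, pulmonary embolism | yes | yes | yes |
| Stroke; cardiac arrest | yes | yes | no |
| Readmission for the mother's health | yes | yes | no |
| Postnatal depression (F53.X) | yes | no | no |

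The register link already exists, so the narrower source for depression comes from the table and not from data access. The table footnote leaves to the final SAP which variables are secondary and which exploratory. It does not leave the source open.

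**Step 2. Does the coverage statement settle it?** Not fully. Close to full coverage, attributed to transfer from hospital charts, speaks to how completely charted hospital events reach the registers. It does not say what share of women with postnatal depression receive an F53.X code in SPR.

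**Step 3. Effect of incomplete capture.** Let p1 and p0 be the true risks (outpatient, inpatient), s the share of cases captured, equal in both arms, with no false positives.

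- Observed risks: s·p1 and s·p0.
- Observed risk difference: s·(p1 − p0), which shrinks in proportion to s.
- Observed risk ratio: (s·p1)/(s·p0) = p1/p0, unchanged.
- Standard error of the log risk ratio with n per arm: √[(1 − s·p1)/(n·s·p1) + (1 − s·p0)/(n·s·p0)], which grows as s falls.

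**Step 4. Illustration.** From the Power calculation section: 8891 randomised with 5% drop-out, so n = 8891 × 0.95 / 2 ≈ 4223 per arm. Assumed, not in the article: p0 = 10%, p1 = 12.5% (risk ratio 1.25), and s from 1.0 down to 0.25.

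| s | Observed risks | Risk difference (points) | Risk ratio | SE of log risk ratio | Expected 95% CI, 1.25 × exp(±1.96·SE) |
|---|---|---|---|---|---|
| 1.0 | 12.5% v 10% | 2.50 | 1.25 | 0.062 | 1.11 to 1.41 |
| 0.8 | 10% v 8% | 2.00 | 1.25 | 0.070 | 1.09 to 1.43 |
| 0.5 | 6.25% v 5% | 1.25 | 1.25 | 0.090 | 1.05 to 1.49 |
| 0.25 | 3.125% v 2.5% | 0.625 | 1.25 | 0.129 | 0.97 to 1.61 |

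The table shows direction and mechanism only. Nothing in the article says which line applies.

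**Step 5. What a second register does.** A case found in either register is counted, so capture from the two together is at least that of SPR alone. The gain may be small or large; the article does not allow it to be sized.

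**The case against.** The strongest defence is that the article shows no loss. It gives no capture rate for F53.X, and SPR does not stop at discharge: it is the sole source for breastfeeding at the midwife visit 8–12 weeks after birth. Register-based retrieval is a stated design choice, and at least one other postpartum row, postpartum fever, also rests on SPR alone. Depressive symptoms are measured anyway with the EPDS. The row is one of dozens of secondary or exploratory variables, and equal under-capture leaves the risk ratio unbiased.

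Most of this stands, and it limits the point to its present size. What it does not answer is why stroke, sepsis and readmission warrant a second, already linked register and depression does not. A midwife visit recorded in SPR makes some later capture plausible, but does not show that a diagnosis made elsewhere would reach SPR.

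Two stronger readings are tempting. One is that most cases are missed. That needs s below 0.5, which the article neither supports nor excludes. The other is that the EPDS should replace the coded outcome. The two measure different things, a symptom score and a recorded diagnosis. The questionnaire is open to non-response in an unblinded trial, and it is already an outcome in its own right. Any power comparison favouring it depends on assumed capture and response rates and on treating the scale as error-free with ignorable non-response. That the two measures may disagree is to be expected and is no contradiction in the plan.

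**Conclusion.** The point holds as a minor one. The source for coded postnatal depression is narrower than for comparable maternal rows without a stated reason, so the outcome may be under-ascertained to an unknown degree. The consequence is a risk difference shrunk by the factor s and some loss of precision, with the risk ratio unchanged. This rests on capture being equal in the two arms and on no false positives; the article gives no information on either. With unequal capture the observed risk ratio would be multiplied by s1/s0, the outpatient share captured over the inpatient share, but nothing in the article indicates that it is unequal. Neither primary outcome is touched.

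**What to change.** In the postnatal depression row of Table 3, and in the SAP when it is finalised:

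- Add the National Patient Register as a source beside SPR. Count an F53.X diagnosis first recorded after delivery and within 12 weeks, so that earlier illness is not counted as an event.
- Use the Prescribed Drug Register, restricted to treatment newly started after delivery, as a supporting analysis only, because the drugs have other indications.
- Keep the three-month EPDS as the separate symptom outcome, adjusted for the baseline EPDS, and report it next to the coded outcome so that readers see both.

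The cost is a change of wording. The register links and the questionnaires are already in place, no new data collection is needed, and the article says the SAP is to be set before data lock.

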Time from start of induction to delivery	Continuous (hours, minutes)		SPR
Duration of stay at the hospital	Continuous (hours, minutes)		SPR
Duration of stay at the hospital before delivery	Continuous (hours, minutes)		SPR
Duration of stay at the hospital after delivery	Continuous (hours, minutes)		SPR
Descriptive outcomes for the outpatient group only			
Delivery within 30 and 60 min from admission to hospital	Dichotomous (yes, no)		SPR
Caesarean section within 60 min from admission to hospital	Dichotomous (yes, no)		SPR
Arrival at the hospital by ambulance	Dichotomous (yes, no)		Ambureg
Delivery before reaching the hospital	Dichotomous (yes, no)		SPR

* The final statistical analysis plan will be set prior to data lock and define which variables will be studied as secondary vs exploratory variables.

Ambureg, the Swedish Ambulance Register; ICD-10, International Statistical Classification of Disease and Related Health Problems, 10th revision; OPTION, Outpatient Induction; PROM, prelabour rupture of the membranes; SCB, Statistics Sweden; SNQ, the Swedish Neonatal Quality Register; SPR, the Swedish Pregnancy Register.

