### Power calculation

Non-inferiority will be tested with a two-sided 95% CI and 80% power. Calculating with 2.8% (based on data from the SPR 2014–2018^5^) for the primary composite outcome in outpatients and 2.3% in inpatients and a 5% drop-out rate, 8891 women need to be randomised to achieve a probability ≥0.80 that the upper limit of a two-sided 95.7% CI for the difference in primary outcome will be less than the non-inferiority margin 1.5%. The vaginal delivery rate was 88% in a group of women fulfilling the eligibility criteria (SPR, 2014–2018^5^). Assuming a vaginal delivery rate of 90% in the outpatient arm, calculating with 80% power, a two-sided 99.3% CI, a non-inferiority margin of 1.5% and a 5% drop-out rate, 2119 women need to be randomised to each arm induced with either balloon catheter or oral misoprostol to assess efficacy of either method in the different IOL settings.

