#### Data analyses

The final statistical analysis plan (SAP) will be set prior to data lock. All main analyses will be performed according to ITT, and complementary analyses will be performed on the per-protocol population. The statistician performing the analyses will be blinded to allocation and primary IOL method.

For comparison between the two allocation groups, Fisher’s exact test will be used for dichotomous variables, Fisher’s non-parametric permutation test for continuous variables, Mantel-Haenszel χ² test for ordered categorical variables and Pearson’s χ² test for non-ordered categorical variables. For all comparisons between the two groups, regarding dichotomous and continuous variables, mean differences with 95% CI will be calculated.

For the primary outcome variable and other dichotomous outcome variables, multivariable binary regression will be used for the adjustment. For continuous variables, analysis of covariance (ANCOVA) will be used for the adjustment.

For dichotomous variables, risk difference with 95% CI and risk ratio with 95% CI will be calculated between the two groups and 95% CIs for the estimated proportions. The distribution of continuous variables as well as change in continuous variables will be given as mean, SD, median, minimum, maximum, and first and third quartiles. Categorical variables will be given as number and proportion. Exploratory analyses will be performed on subgroups stratified for parity (primiparous vs multiparous women), initial method of IOL (balloon catheter vs oral misoprostol), Bishop score in women without PROM (<3 versus ≥3), indication for IOL (PROM vs other than PROM) and reported travel time to the hospital (<30 min and ≥30 min).

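### Time from start of induction to second stage has no value for women delivered by caesarean before second stage, yet it falls under a mean-difference and ANCOVA analysis by intention to treat

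*Protocol article*

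**What the plan says.** Table 3, under time variables, lists "Time from start of induction to second stage of delivery" as continuous, in hours and minutes, taken from the pregnancy register. No denominator is given, and nothing is said about women who never reach second stage. The next row, "Time from start of induction to delivery", has a value for every woman who gives birth.

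The Data analyses section sets methods by variable type. For continuous variables it names a "non-parametric permutation test for continuous variables". It adds: "For all comparisons between the two groups, regarding dichotomous and continuous variables, mean differences with 95% CI will be calculated." For adjustment: "For continuous variables, analysis of covariance (ANCOVA) will be used for the adjustment." On the population: "All main analyses will be performed according to ITT", with per-protocol analyses as a complement. No time-to-event or competing-event method is named.

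The status of the variable is open. The footnote to Table 3 states: "The final statistical analysis plan will be set prior to data lock and define which variables will be studied as secondary vs exploratory variables."

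The rates used for sizing come from the Power calculation section: "The vaginal delivery rate was 88% in a group of women fulfilling the eligibility criteria", with 90% assumed for the outpatient arm. Primary outcome 2 (Table 2) is the proportion of vaginal births.

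**The concern.** A mean and an ANCOVA need a number for each woman. A woman whose caesarean comes before second stage has none, so the prescribed analysis cannot include all randomised women for this variable. What remains is a comparison of those who reached second stage, and reaching it is decided after randomisation.

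If slow inductions are more likely to end in caesarean, each arm's mean is computed after some of its slowest women have been removed. If one arm has more caesareans, more of its slow women go, and its mean looks shorter although nobody progressed faster. The direction is perverse: a worse caesarean result would come with a better-looking duration result. A reported difference in speed could then not be separated from a difference in caesarean rate.

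**Working it through.** **Number of women in the analysis.** The article gives no figure for this outcome, so I first reproduced its total of 8891 to obtain the evaluable number. Inputs (Power calculation): composite outcome 2.8% outpatient and 2.3% inpatient, margin 1.5 points, 95.7% confidence interval (one-sided 0.0215), 80% power, 5% drop-out. The Farrington-Manning formula is

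n per arm = (z₁√V₀ + z₂√V₁)² / (0.015 − 0.005)²

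with z₁ = 2.0237, z₂ = 0.8416, V₀ = 0.052166 (restricted estimates 1.936% and 3.436%) and V₁ = 0.049687. This gives 4222.6, so 4223 per arm. Then 2 × 4223 = 8446, and 8446 / 0.95 = 8890.5, which rounds up to the stated 8891.

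**Women without a value.** Caesareans at the planned rates: 0.12 × 4223 = 507 inpatient and 0.10 × 4223 = 422 outpatient, 929 in all. The share before second stage is an assumption:

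| Assumed share before second stage | Women without a value | % of 8446 | Inpatient v outpatient |
|---|---|---|---|
| 50% | 465 | 5.5% | 6.0% v 5.0% |
| 80% | 743 | 8.8% | 9.6% v 8.0% |
| 100% | 929 | 11.0% | 12% v 10% |

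**Spurious difference, first model.** All inputs except the caesarean rates are assumptions. Underlying time is log-normal with mean m and the same in both arms. A latent tendency to caesarean before second stage has correlation ρ with log time, and a fraction q = (share × caesarean rate) is excluded. The mean among the rest is

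m × Φ(c − ρσ) / (1 − q), with c = Φ⁻¹(1 − q) and σ² = ln(1 + (SD/m)²).

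Example: m = 24 h, SD 12 h (σ = 0.4724), share 80%, ρ = 0.5.
- Inpatient: q = 0.096, c = 1.3047, Φ(1.0685) = 0.8574, mean 24 × 0.8574 / 0.904 = 22.76 h.
- Outpatient: q = 0.080, c = 1.4051, Φ(1.1689) = 0.8788, mean 24 × 0.8788 / 0.920 = 22.92 h.
- Difference 0.163 h, or 9.8 minutes, with no true difference.

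Outpatient minus inpatient, in minutes, at 12% v 10% caesarean:

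| Mean (SD), h | Share | ρ = 0 | ρ = 0.5 | ρ = 0.9 |
|---|---|---|---|---|
| 24 (12) | 50% | 0 | 6.9 | 13.3 |
| 24 (12) | 80% | 0 | 9.8 | 18.2 |
| 24 (12) | 100% | 0 | 11.5 | 21.1 |
| 30 (15) | 50% | 0 | 8.6 | 16.6 |
| 30 (15) | 80% | 0 | 12.2 | 22.8 |
| 30 (15) | 100% | 0 | 14.4 | 26.4 |

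Simulation of the last setting gave 26.7 minutes, hence the upper end of 27. With equal rates (12% v 12%) every entry is 0. With outpatient caesareans higher by the margin (13.5% v 12%), the sign reverses: −5 to −19 minutes for ρ of 0.5 to 0.9.

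**Second model.** Log-normal time with median 22 h and log-SD 0.55, caesarean probability logistic in log time with a log-odds slope of 0.5 to 1.5 per SD, shares of 50% to 100%, and 4223 per arm. At 12% v 10% the spurious difference is 0.06 to 0.33 h (4 to 20 minutes), and a nominal 5% test rejects 5% to 21% of the time. At 12% v 13.5% it is −0.05 to −0.24 h (−3 to −14 minutes).

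**The case against.** The strongest reply is that the statistical analysis plan is still to be set before data lock. The denominator of one row in a long table is the kind of detail an article leaves to it, and the Data analyses paragraph is generic and never says that women without a value are dropped. It is true that the later plan may settle this. But the article does more than stay silent: it assigns continuous variables a method that cannot be carried out for this one in all randomised women. A plan that follows it inherits the problem.

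Second, Table 3 already has vaginal delivery within 24 and 48 hours. These are defined for every woman and count a caesarean as no success. That stands and limits the harm, although these rows measure vaginal birth and not second stage.

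Third, the effect is minutes on a mean of about a day. That also stands.

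Several stronger readings are tempting but unsupported:
- A reader might infer that most caesareans drop out. The article does not give the share before second stage.
- A reader might infer that the analysis conditions on primary outcome 2. It conditions on reaching second stage, and a caesarean in second stage keeps its value.
- A reader might call this a flawed secondary outcome. Secondary or exploratory status is deferred.
- A reader might say that time to delivery has the opposite flaw, because caesarean ends the clock. That is its definition. It exists for every woman, measures total duration and also serves the health economic analysis.

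**Conclusion.** The point holds as a minor one. The method named for continuous variables does not fit time to second stage, because the women it can use are a post-randomisation subset related to primary outcome 2. The ceiling on women without a value, about 11%, follows from the planned rates. The lower figure of 5.5% rests on an assumed share of caesareans before second stage.

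The spurious difference of roughly 4 to 27 minutes rests on assumed time distributions, an assumed link between slow progress and caesarean, and the planned two-point difference in caesarean rates. It vanishes if there is no such link, or if rates and selection are the same in both arms. The upper rejection rate of 21% belongs to the most unfavourable setting of the second model and should not be read as the expected error rate. No primary outcome, margin or sample size is touched.

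**What to change.** In the final analysis plan, make the between-arm comparison the cumulative incidence of second stage from start of induction in all randomised women, with caesarean before second stage as a competing event. Report the difference at fixed times such as 24 and 48 hours. Follow-up is nearly complete, so this comes close to the proportion of all randomised women who had reached second stage by each time, for which the article's risk difference and confidence interval already serve.

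Report mean or median time to second stage only descriptively, among women who reached it, with the denominator by arm. Separate an unrecorded second-stage time from a second stage that never occurred.

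Keep time to delivery as a total-duration measure for all women, and read it with mode of delivery and the 24- and 48-hour vaginal delivery rows. The description of the 48-hour row in Table 3 repeats the 24-hour limit and should be reconciled before it is relied on.

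The cost is wording and a little analysis. Delivery time and mode are already collected. The drawback is a result less simple than a mean difference in hours.
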